## 4.2. Exclusion criteria

- 1) Patients whose participation in the research is considered to be difficult because of a psychiatric disorder or psychiatric symptoms that impair daily life.
- 2) Patients with active infections that require systemic treatment.
- 3) Patients with a complicating active digestive tract ulcer.

- 4) Patients with complicating interstitial lung disease or pulmonary fibrosis diagnosed by imaging findings or clinical findings, or with a history thereof.
- 5) Patients with imaging tests showing an interstitial shadow, or with inflammatory changes in the lungs such as active radiation pneumonitis or infectious pneumonia.
- 6) Patients who test positive for any of HIV antibodies, HTLV-1 antibodies, HBs antigens, HCV antibodies (however, even if positive for HCV antibodies, patients with no HCV-RNA detected will not be excluded). All of these require confirmation via blood test.
- 7) Patients who are negative for HBs antigens, positive for HBs antibodies or HBc antibodies, and positive for HBV-DNA quantification (the patient may be enrolled if the result is below the detection sensitivity). However, if the history of hepatitis B vaccination can be confirmed in writing, HBV-DNA quantification is not required.
- 8) Female patients who are pregnant, breastfeeding (cannot be enrolled even if breastfeeding is discontinued), or can become pregnant.
- 9) Any patient deemed ineligible by the principal investigators or co-investigators (including when the attending physician deems the patient to be unsuitable due to individual drug characteristics).

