#### 8.2.2. Tests performed within 14 days before enrollment

The following measurements are made to confirm safety.

- 1) ECOG Performance Status (PS) (If the patient is younger than 15 years of age and evaluation by ECOG is difficult, the performance status scale/score conversion table (Appendix) should be

used to confirm that the patient's performance status is equivalent to 0 or 1 on the ECOG scale.)

- 2) Hematology test: leukocyte count, differential leukocyte count (neutrophils, lymphocytes), hemoglobin, and platelet count
- 3) Blood biochemistry test: albumin, total bilirubin, AST, ALT, creatinine, sodium, potassium, LDH, calcium (albumin correction\*)

\* When serum albumin level is  $\leq 4.0$  g/dL, use the following correction(12)

Corrected calcium (mg/dL) = serum calcium level (mg/dL) + (4-serum albumin level)

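### Exclusion 7 waives the HBV-DNA test on written proof of vaccination without saying which antibody pattern the waiver covers, so an HBc-antibody-positive patient can be enrolled without the result the criterion depends on

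*Protocol*

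**What the plan says.** Hepatitis B eligibility is set in two items of Protocol section 4.2.

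- Item 6 excludes on the surface antigen, alongside other viruses: "Patients who test positive for any of HIV antibodies, HTLV-1 antibodies, HBs antigens, HCV antibodies". It requires a blood test for confirmation.
- Item 7 deals with patients who pass the antigen test but carry an antibody. It excludes "Patients who are negative for HBs antigens, positive for HBs antibodies or HBc antibodies, and positive for HBV-DNA quantification". A parenthesis gives the way in: "the patient may be enrolled if the result is below the detection sensitivity". A further sentence then lifts the test for some patients: "However, if the history of hepatitis B vaccination can be confirmed in writing, HBV-DNA quantification is not required".

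Item 9 of the same section lets the site exclude at its own discretion: "Any patient deemed ineligible by the principal investigators or co-investigators".

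The blood tests scheduled within 14 days before enrolment (section 8.2.2) are a blood count and this panel: "Blood biochemistry test: albumin, total bilirubin, AST, ALT, creatinine, sodium, potassium, LDH, calcium". Section 8.2.3 repeats both within 7 days before treatment. Neither list contains a hepatitis B marker or HBV-DNA.

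**The concern.** Item 7 treats the two antibodies as separate triggers for the same DNA check. The waiver that follows does not keep them apart. Its natural rationale is that a vaccination record explains why the antibody is there, so further testing adds nothing. That works for an isolated HBs antibody, which vaccination with surface antigen produces. It does not work for an HBc antibody, which points to past infection. The waiver's reason thus covers one trigger, while its wording covers both.

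Two things are at stake. The first is the safety screen itself: a patient with undetected viraemia could start an off-label anticancer drug although item 7 is written to keep such patients out. The second is clarity of status. If viraemia at entry came to light after dosing, the first sentence would point to ineligibility, and section 12.1.2 removes patients found ineligible afterwards from the full analysis set. Yet the site would have followed the waiver correctly, so the classification would be arguable.

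**Working it through.** No arithmetic applies, and the plan states no figure on this point. The check is to apply item 7 as written to each kind of patient it addresses, and then to see whether any other provision restores the waived test.

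**Step 1. The rule as logic.** Exclude if HBs antigen is negative AND (HBs antibody is positive OR HBc antibody is positive) AND HBV-DNA is positive. The third term can be evaluated only if a DNA result exists. The waiver drops the requirement to obtain that result when a vaccination record is held, and sets no condition on the second term.

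**Step 2. Apply it.** All patients below are HBs-antigen negative.

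| Antibody pattern | Vaccination record | DNA test required? | Does the record explain the antibody? |
|---|---|---|---|
| HBs antibody only | No | Yes | No record held |
| HBs antibody only | Yes | No | Yes |
| HBc antibody positive | No | Yes | No record held |
| HBc antibody positive | Yes | No | No |

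The fourth row is the problem. It differs from the third only in the record, and the record does not account for the HBc antibody. If that patient is in fact viraemic, the first sentence of item 7 describes an excluded patient, but the site has no obligation to obtain the result that would show it.

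**Step 3. Look for another provision that closes the gap.**

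- Section 4.2, item 6: the only hepatitis B marker is the surface antigen. The fourth-row patient is antigen negative and passes.
- Sections 8.2.2 and 8.2.3, and the study calendar in section 8.6: no hepatitis B test is listed. Section 4.2 is therefore the only visible place that calls for one, which makes the wording of its waiver decisive.
- Section 4.1, item 16: limits on AST, ALT and bilirubin apply, but these are not tests for viraemia. A patient can be within them and still have detectable HBV-DNA.
- Section 4.2, item 9: discretion to exclude, with no duty to test.
- Section 8.3.1: on-treatment safety tests follow each drug's package insert, with no uniform schedule in the protocol.
- Sections 5.2.1 and 5.2.2: sites enrol by confirming the listed criteria in the EDC system, so the literal text is what they apply.

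**Result.** As written, a vaccinated HBc-antibody-positive patient can be enrolled with no HBV-DNA result, and nothing else in the document requires one.

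**The case against.** The best reply is that item 7 contains no contradiction. It states a rule and then an exception, and the exception only lifts a testing requirement. This stands. A reader might infer that the waiver makes HBV-DNA-positive patients eligible; it does not. A known positive result still excludes, and a test that is not required is not forbidden.

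Second, the protocol nowhere says what an HBc antibody signifies or what a vaccine can explain. That step is general serology, brought from outside the document. This also stands as a limit. Without it the text shows only a waiver wider than it needs to be, although it remains true that the parenthesis makes entry depend on a DNA result that the waiver then makes optional.

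Third, other provisions narrow the exposure: the antigen screen, the liver-function limits, the exclusion of active infection needing systemic treatment, investigator discretion, and whatever the package inserts require. This is fair, but none of those visible in the protocol restores the waived test, and the package inserts are not in the document.

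Fourth, the intention is easy to guess: spare the test where vaccination explains the antibody. Probably so, but the sentence does not say it.

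A reader might also infer a distortion of the safety results, through misattributed hepatic events or through the rule in section 12.7.1 that two treatment-related deaths bring a cohort to committee review. The documents do not support that. Adverse-event incidence in section 12.2.2 is counted whatever the cause; section 7.2.2 requires comorbidities to be weighed before an event is called related; and any single treatment-related death is one of the two, so the argument says nothing particular about this clause.

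**Conclusion.** The point holds as a defect of wording in an eligibility safety screen. The waiver in item 7 does not state which antibody-positive patients it covers. Its literal reach includes HBc-antibody-positive patients, and for them it removes the only test in the protocol that would reveal the excluded condition.

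Its size is limited. It concerns HBs-antigen-negative, HBc-antibody-positive patients who hold written proof of vaccination, and actual harm would need such a patient to be viraemic and not tested anyway. The protocol gives no frequency for any of these steps. The group is probably small, and the conclusion does not depend on its size. The primary endpoint, sample size, Table 12.4 and all decision thresholds are unaffected.

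The conclusion rests on two assumptions: that sites apply the sentence as written, and that a vaccination record does not explain an HBc antibody. It should be corrected because the screen can be bypassed by following the protocol to the letter; it does not undermine the statistical design.

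**What to change.** Reconcile the two sentences of section 4.2, item 7. The waiver should state explicitly which antibody-positive patients it covers, and should not remove HBV-DNA quantification for patients the first sentence is meant to screen. Where that line falls is a clinical rule for the sponsor to settle; no wording is proposed here.

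The cost is one clause in the protocol, through the change procedure in section 13.9, with the eligibility check at enrolment aligned to it. If the waiver is narrowed, a few vaccinated patients would need an HBV-DNA test that item 7 already names. No statistical section has to change.

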## 5. Enrollment

### 5.1. New participation procedure (in the case of the first patient in each study center)

#### 1) Procedures under the Clinical Research Act

The Study Representative Physician/Study Secretariat will apply to the Certified Clinical Research Review Board for a change in the research plan (addition of a study center). If approval is obtained, the application is submitted for deliberation at the Patient-Proposed Healthcare Service Evaluation Committee. Based on the results of the deliberation, the addition will be published in the jRCT after obtaining the approval of the director of the relevant study site.

#### 2) Applications based on the patient-proposed healthcare service system

Study centers wishing to participate in this research should ensure that they meet the requirements of “15.1.1. Requirements for study centers,” and fill out and send in the Patient-Proposed Healthcare Service Notification Form.

The Coordination Office will confirm the content of the notification form, and after obtaining approval from the Study Representative Physician and the Study Secretariat, the Central Hospital Patient-Proposed Healthcare Service Committee of the National Cancer Center Hospital, which is a clinical research core hospital under medical law, will be asked to examine whether or not the medical institution should participate in this research. If approval is obtained from the Central Hospital Patient-Proposed Healthcare Service Committee, the Coordination Office will notify the local Public Welfare (Branch) Office within seven days of the approval. Thereafter, the Minister of Health, Labour and Welfare will send a notification on the decision to add the relevant medical institution to the study centers. The Coordinating Office will confirm that the Minister of Health, Labour and Welfare has issued notification of the decision and will contact the principal investigator of the study center.

#### 3) Procedures for conducting this study

Prior to the start of patient enrollment, it is necessary to conclude a written contract that defines the roles of both parties in this research between the National Cancer Center Hospital, which is the main research institute, and the study center

Each study center will start enrollment of the first patient upon completion of the three procedures above (see “5.2 Patient Enrollment”).

### 5.2. Patient enrollment (in the case of the second and later patients in each study center)

When the patient is the second or later patient in each study center, patient enrollment will be performed according to the procedure shown below

#### 5.2.1. Enrollment procedure

The principal investigator or co-investigator will confirm that the subject patient meets all the eligibility criteria and does not meet any of the exclusion criteria, and will then enroll the patient using electronic data capture (EDC).

The URL and procedures will be notified separately in the “EDC Input Manual.”

Patient enrollment number    1901-    Y/N - ○○○ -    ...  
                                          [Trial number]-[presence of target lesion]-[Medication name]-[Serial number]

(Contact person for questions relating to patient selection criteria)

Study secretariat

[name]

Department of Medical Oncology, National Cancer Center Hospital

[name]

[contact] ([name])

[contact]

Email : [contact]

[name]

Department of Pathology and Clinical Laboratories, National Cancer Center Hospital  
[name]

[contact] ([name])

[contact]

Email: [contact]

(Contact person for questions relating to patient enrollment and EDC)

Data Management Supervisor

Data Management Office, Data Management Section, National Cancer Center  
Hospital

[name]

[contact] ([name])

[contact]

Email: NCCH1901\[contact]

Weekdays 9am–5pm (excluding Saturday, Sunday, holidays, and New Year holiday)

### **5.2.2. Cautions during enrollment**

- 1) Eligibility confirmation is performed on the enrollment screen.
- 2) Enroll the patient after confirming that he/she is not the subject of a sponsor-initiated clinical trial or an investigator-initiated clinical trial or for advanced medical treatments at a study center in Japan. However, the patient may participate in the present study if there is a justifiable reason that it is difficult to participate in these other clinical trials, such as geographical reasons. In such a case, state the reason in the EDC.
- 3) When the input data are insufficient, the enrollment will not be accepted until all requirements are satisfied.
- 4) After eligibility has been confirmed in EDC, an enrollment number will be issued and enrollment will be completed.
- 5) Patients will not be disenrolled (deleted from the database) except in the case of withdrawal of consent, including refusal for the data to be used for research.

Contact the Study Secretariat promptly when an incorrect enrollment is found

### **5.3. Procedure for the completing enrollment for each drug**

If it is anticipated that the planned number of enrollments will be achieved in each drug cohort, the Study Representative/Study Secretariat will inform the Principal Investigator of the achievement of the number of enrollments and issue precautions for future patient enrollment.

## 6. Treatment planning and treatment change criteria

### 6.1. Protocol treatment

Treatments and treatment changes should be performed as described in this chapter unless patient safety is threatened. Promptly start the protocol treatment as soon as the drug is received. Use the drug selected according to 2.2.4 as the protocol treatment. Start the treatment after an appropriate interval from the previous treatment according to the package insert.

#### 6.1.1. Chemotherapy

##### 1) Treatment regimen

The treatment regimen (dosage and administration) for each medicinal product is as described in the latest edition of the package insert.

Combination with cytotoxic chemotherapeutic drugs is not permitted in this study even if combination with other drugs is permissible according to the package insert. When single agents are used in combination with other medicines, follow the dosage and administration from the package insert. The drugs that can be used in combination in this study are defined according to “19. Appendix: List of medicines.”

For each drug, changes such as delays (prolongation of dosing interval, delaying administration more than what is prescribed), pauses (temporary suspension or withdrawal that can resume if certain conditions are met), and supportive care and concomitant use contraindications, etc. should comply with the package insert.

The package inserts can be obtained from the search page of the Japan Pharmaceuticals and Medical Devices Agency.

Pharmaceutical product information search page: <http://www.pmda.go.jp/PmdaSearch/iyakuSearch/>

##### 2) Calculating the administered dose

For pharmaceuticals for which the dose is defined by body weight or body surface area, the initial dose is calculated using body weight or body surface area recorded at enrollment.

As a rule, the actual dose of each medicine is rounded off to two significant figures.\* The amount administered should not exceed the maximum dose specified in the package insert.

For pediatric patients less than 15 years of age, body surface area should be calculated using the Mosteller formula.

Body surface area [ $\text{m}^2$ ] =  $\sqrt{(\text{height}[\text{cm}] \times \text{body weight} [\text{kg}]) / 3,600}$

\* Two significant figures: calculate with reference to the following example

When the amount is calculated in terms of body surface area or weight, proceed as follows:

Example 1)  $134 \text{ mg} = 1.34 \times 10^2 \rightarrow$  round down the 4  $\rightarrow$  130 mg is the actual dose

Example 2)  $0.85 \text{ mg} = 8.50 \times 10^{-1} \rightarrow$  round down the 0  $\rightarrow$  0.85 mg is the actual dose

## 6.2. Criteria for discontinuing/terminating the protocol treatment

### 6.2.1. Definition of terminating the protocol treatment

Since the protocol treatment is to be continued until the protocol treatment discontinuation criteria are met, there is no definition for terminating the protocol treatment. If the upper limit of the total administration period for each drug is stated in the package insert, observe this limit.

### 6.2.2. Criteria for discontinuing the protocol treatment

The protocol treatment should be discontinued if any of the following is true.

- 1) When it is determined that the protocol treatment is ineffective according to any of the following
  - ① If a marked increase in the lesion was observed after starting treatment, and it was determined necessary to change treatment.  
If it is determined that continuing the protocol treatment is clinically appropriate even if it is determined as “progressive disease” (PD) by the response evaluation from imaging, the protocol treatment is continued and not discontinued.
  - ② If a deterioration of clinical symptoms determined to be due to disease progression is observed
- 2) If the protocol treatment cannot be continued due to an adverse event
  - ① When a Grade 4 adverse event is observed (except for the following events)
    - Hematologic toxicity: anemia, hypocellular marrow, lymphocyte count decrease, neutrophil count decrease, leukocytopenia, platelet count decrease, or CD4 lymphocytopenia according to the “Japanese translation JCOG version of the NCI Common Terminology Criteria for Adverse Events v 5.0 (CTCAE v5.0)” (hereinafter, CTCAE v5.0-JCOG) (13)
    - Non-hematologic toxicity: Alkaline phosphatase increase, GGT increase, high cholesterol, hypertriglyceridemia, hyperuricemia, and transient electrolyte abnormality according to the CTCAE v5.0-JCOG

For an adverse event which was not related to the protocol treatment, if the event was improved or recovered and the restarting the protocol treatment was considered to be profit for the patients, the Principal Investigator or the Co-investigator can discuss the restarting with the Study Representative/Study Secretariat.
  - ② If it was determined that the Principal Investigator or Co-investigator would need to discontinue the protocol treatment due to an adverse event that does not fall under [1] above
- 3) If the patient requests that the protocol treatment be discontinued because an association with the adverse event cannot be ruled out
  - Use this classification if the association with the adverse event cannot be denied
- 4) If the patient requests that the protocol treatment be discontinued because of the reason(s) that an association with the adverse event cannot be ruled out
  - ① In case of refusal by the patient before starting protocol treatment after enrollment
  - ② If the association with adverse events cannot be ruled out because of the relocation of the person or family member during protocol treatment
- 5) Death during the protocol treatment
  - Death before deciding to discontinue protocol treatment for other reasons
- 6) Additional reasons include exacerbation before the start of treatment after enrollment (could not start the protocol treatment due to rapid exacerbation), a protocol violation was found, an ineligibility was discovered due to a change in the pathologic diagnosis after enrollment and treatment was changed, etc., or it is determined that continuation of the protocol treatment is difficult due to social reasons or safety management problems

The protocol discontinuation date is the death date in case of 5), or the day when the Principal Investigator or the Co-investigator determines the subject to be ineligible after enrollment; otherwise it is the day when the Principal Investigator or the Co-investigator determines that the protocol treatment should be discontinued.

### **6.3. Post-treatment**

In the present study, the post-treatment after discontinuing the protocol treatment is not particularly defined, but the following post-treatment can be assumed.

1. Participation in patient-proposed healthcare services for medications for other different genetic mutations obtained from the initially submitted specimens
2. Participation in patient-proposed healthcare services for the same type of medication for the same genetic abnormalities
3. Conducting some form of chemotherapy for practical diagnosis and treatment
4. Participation in other clinical trials and studies
5. Follow-up observation/best supportive care, etc.

## 7. Expected adverse events

### 7.1. Adverse reactions expected with the drug

The adverse reactions expected for each drug in this study are different. For this reason, refer to the latest edition of the package insert for the adverse reactions expected for the drugs used in protocol treatment.

### 7.2. Evaluating adverse events/adverse reactions

Use the “Japanese translation JCOG version of the NCI Common Terminology Criteria for Adverse Events v 5.0 (CTCAE v5.0)” (hereinafter, CTCAE v5.0-JCOG) to evaluate the adverse events/adverse reactions in this study. Regarding the parameters for which grades are defined as the laboratory standard value in the CTCAE v5.0-JCOG, the “JCOG Common Standard Reference Range” is used instead of the in-house standard value for each medical institution. Refer to the JCOG website (<http://www.jcog.jp/doctor/tool/kijun.html>) for details on the “JCOG Common Reference Range.” For children under 15 years of age, abnormalities in laboratory test values listed in the CTCAE Grade Definition Table for Pediatric Clinical Reference Ranges (Appendix) should be graded by using the Appendix, and the event should be recorded in the eCRF Adverse Event Form.

